## Method and design

### Study design

This study is a multicenter RCT comparing an acupuncture plus auricular acupressure (AA) treatment group with a Climen® (Bayer Healthcare Company Limited, Guangzhou, China) control group (Figure 1, Table 1). Two hundred and six participants will be included from the following three hospitals in Chengdu, Sichuan, China: First Affiliated Hospital of Chengdu University of Traditional Chinese Medicine (TCM), Chengdu Integrated TCM & Western Medicine Hospital, and General Hospital of Chengdu Military Region of the Chinese People’s Liberation Army.

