### Patients

#### Study population and sample size

This study focuses on women experiencing perimenopausal syndrome. According to the previous study by Guang’anmen Hospital, China Academy of Chinese Medical Sciences (results still unpublished), the improvement of Menopause Rating Scale (MRS) scores of the electro-acupuncture group and the sham acupuncture group were 6.5 and 2, respectively. The difference in scores between the two groups was 4.5, and electro-acupuncture was not superior to sham acupuncture. Accordingly, we assume that a difference within 4.5 indicates acupuncture is not inferior to Climen® treatment. Using a non-inferiority design, and assuming a power of 90%, an alpha value of 5%, and a population standard deviation of 10, a total of 206 patients will be needed in this study. Each group needs 103 patients (assuming a 20% dropout rate).

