### Statistical analysis

All data from this study will be analyzed by special analysts with SPSS 20.0 (IBM Corp., Armonk, NY, USA).

The tests of outcomes are based on the intention-to-treat population. Sensitivity analyses are performed for the primary outcomes (MRS measured 16 weeks after randomization) by replacing missing data with multiple imputations and lost observations carried forward using SPSS 20.0. Multiple imputations are calculated using the propensity score method. The MRS is used as a dependent variable in an analysis of covariance, with the groups as random factors, and with baseline MRS and age as covariates, to account for potential baseline differences. Adjusted mean treatment effects are given alongside corresponding 95% confidence intervals and *P* values. The same analysis method will be performed for all secondary outcomes.

In addition to the above analysis, we will perform an exploratory analysis to describe group means over time. We will calculate summary statistics to reveal whether the two groups are changing in a similar or different fashion. A two-sided test is applied for available data, and *P* < 0.05 is considered statistically significant.

There is one acupuncturist in each center to do all treatment, which probably introduces a clustering effect in this trial. We therefore calculated the intracluster correlation coefficient from the result of this trial and report the coefficient [28].

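### The ANCOVA labels the two treatment arms a random factor, and the clustering by acupuncturist that the plan expects is reported as an ICC but not reflected in the confidence interval

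*Protocol article*

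**What the plan says.** All but two of these statements are in the Statistical analysis section of the protocol article.

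- **Model:** an analysis of covariance of the MRS "with the groups as random factors, and with baseline MRS and age as covariates". No centre or acupuncturist term is named.
- **Output:** "Adjusted mean treatment effects are given alongside corresponding 95% confidence intervals", together with P values.
- **Clustering:** "There is one acupuncturist in each center to do all treatment, which probably introduces a clustering effect in this trial". The response is "We therefore calculated the intracluster correlation coefficient from the result of this trial and report the coefficient".
- **Secondary outcomes:** "The same analysis method will be performed for all secondary outcomes".
- **Centres** (Study design): "Two hundred and six participants will be included from the following three hospitals in Chengdu, Sichuan, China".
- **Margin** (Study population and sample size): "we assume that a difference within 4.5 indicates acupuncture is not inferior to Climen® treatment". That section assumes an SD of 10, 90% power, alpha 5% and 20% dropout, and arrives at 103 per arm. It mentions no allowance for clustering.

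**The concern.** Three things in the model statement do not fit the plan's own purpose.

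1. A factor is random when its levels stand for a wider set of possible levels. The two arms do not; their difference is the question of the trial. A model that treats group as random estimates a between-group variance from two levels, and the treatment difference is then a shrunken prediction without an ordinary CI. That conflicts with the promised adjusted effect and 95% CI.

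2. The plan names a source of correlation and then leaves it out of the interval. Only the AA arm is treated by the acupuncturists, and each acupuncturist coincides with a centre. Any difference between acupuncturists is therefore a difference in treatment effect between centres. If such differences exist and the conclusion is meant to reach other acupuncturists, the interval is too narrow. In a trial sized on a non-inferiority margin, a too-narrow interval makes success easier.

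3. Read literally, the statement on secondary outcomes carries baseline MRS into the models for the hormones, MENQOL and hot-flash score, although Table 1 gives each of these its own baseline measurement. This is a smaller matter of precision.

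**Working it through.** **Inputs from the article:** margin 4.5; SD 10; 103 per arm; 20% dropout; 3 centres with one acupuncturist each. **Assumptions:** equal numbers per centre, clustering in the AA arm only, and ICC values from 0 to 0.10, because the article gives none.

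**The plan's own sample size.** With one-sided alpha 5%, 90% power and a true difference of 0, n per arm = 2 × [10 × (1.645 + 1.282) / 4.5]² = 84.6, so 85 (86 with the t distribution). Then 86 × 1.2 = 103.2, which gives 103 per arm and 206 in total. The figure is reproduced without any design effect.

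**Random group.** In a mixed model with two group means, the predicted difference is about d × (1 − SE²/d²). With 82 evaluable per arm (103 × 0.8 = 82.4), SE = 10 × √(2/82) = 1.56 and SE² = 2.44.
- Observed 4.5: 4.5 × (1 − 2.44/20.25) = 3.96.
- Observed 2.0: 2.0 × (1 − 2.44/4) = 0.8.

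Fits to three simulated data sets show the same pattern: fixed-effect estimates of −1.56, 1.49 and 5.96 became predicted differences of −0.50, 0.44 and 5.69. In a classical one-factor ANCOVA, by contrast, the test uses the same residual error under either label, and the difference and its CI need not change.

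**Clustering in the AA arm.** There are m = 82/3 = 27.3 women per acupuncturist. Design effect DE = 1 + (m − 1) × ICC. SE ratio k = √[(DE + 1)/2]. The one-sided error of the unadjusted 95% CI when the true difference equals the margin is 1 − Φ(1.96/k), and coverage is 2Φ(1.96/k) − 1.

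| Assumed ICC | DE | k | Error at margin | Coverage | Half-width allowing for clustering |
|---|---|---|---|---|---|
| 0 | 1.00 | 1.00 | 2.5% | 95% | 3.06 |
| 0.01 | 1.26 | 1.06 | 3.3% | 93.5% | 3.26 |
| 0.02 | 1.53 | 1.12 | 4.1% | 92% | 3.44 |
| 0.05 | 2.32 | 1.29 | 6.4% | 87% | 3.94 |
| 0.10 | 3.63 | 1.52 | 9.9% | 80% | 4.66 |

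The last column treats the ICC as known. With all 103 per arm (m = 34.3) the errors are somewhat larger: 4.5% at ICC 0.02 and 7.4% at 0.05.

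**Power at a true difference of 0, ICC 0.05, one-sided 2.5%.** True SE = 1.56 × 1.288 = 2.01.
- Unadjusted CI: Φ[(4.5 − 3.06)/2.01] = 76%.
- CI widened for clustering: Φ(4.5/2.01 − 1.96) = 61%.
- No clustering: 82%.

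The 6.4% error belongs to the unadjusted CI and the 61% power to the widened one; no single analysis has both.

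**Does a centre main effect repair it?** Simulation of 4,000 trials per setting, 103 per arm, true difference 4.5:
- Centres differ (ICC 0.05 to 0.10), acupuncturists do not, centre omitted: mean estimate 4.45 to 4.46, coverage 95.0%, error 2.6% to 2.8%.
- Acupuncturist ICC 0.05: error 7.3% without centre and 7.1% with it; coverage 84.6% and 84.8%; mean estimate 4.56 in both.

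**The case against.** The strongest defence is that the section names an analysis of covariance and promises an ordinary adjusted effect with a CI. The word random may then be no more than a slip: in a one-factor ANCOVA the label need not change the result. That stands. A reader might infer that the planned effect estimate is wrong or shrunk towards non-inferiority; the article does not support this. It names no mixed model, and shrinkage in such a model works in both directions: −1.56 became −0.50, which moves a result favouring AA towards the margin. What remains is a specification with two readings that give different results.

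A reader might also infer that leaving out centre biases the effect or spoils its interval. The simulation shows neither. Centre is worth adding because it costs little and allows the effect to be shown by centre, not because its absence invalidates the CI.

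The clustering figures presuppose acupuncturists drawn from a wider population. If inference is limited to these three, or the ICC is 0, they do not apply. That stands too, but the article does not state such a limit, and its Discussions section describes the parent programme as aiming at guidelines for clinical practice.

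Finally, the reference to the same method for secondary outcomes can be read as ANCOVA with the matching baseline. That is a fair reading, so this part is only a request for clarity. The article also states no rule comparing the CI with 4.5; that is a separate matter.

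**Conclusion.** The point holds in a limited form. Group should be a fixed factor, because the plan's stated output is a treatment contrast; whether the present wording would alter the numbers depends on how the model is fitted. The expected clustering is acknowledged but not carried into the CI, and an ICC estimated from three clusters cannot fill that gap. If the acupuncturist ICC in the AA arm is 0.02 to 0.05, the unadjusted 95% CI read against 4.5 has a one-sided error of about 4.1% to 6.4% instead of 2.5%. This rests on an assumed ICC, equal centres, 82 evaluable per arm, SD 10, and a conclusion meant to reach beyond the three acupuncturists. The estimate itself stays essentially unbiased. The matter should be put right, but it does not invalidate the trial.

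**What to change.** - Specify group as a fixed factor and add centre as a fixed factor with 3 levels, keeping baseline MRS and age as covariates.
- Report the AA minus Climen difference by centre from a group-by-centre term. A centre main effect alone does not deal with the clustering.
- Then do one of two things: state that the conclusion is limited to these three acupuncturists, or add a sensitivity CI widened for a stated range of assumed acupuncturist ICCs in the AA arm (for example, the values in the table). Assumed values are preferable to the trial's own ICC, which three clusters cannot pin down.
- State that in each secondary model the outcome's own baseline replaces baseline MRS.

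The cost is a few lines of text and 2 to 4 degrees of freedom, with no new data. The possible downside is a wider sensitivity interval: at ICC 0.05 the half-width rises from 3.06 to 3.94.

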The total observation period within this study is 37 weeks, including 1 week of baseline, 12 weeks of treatment and 24 weeks of follow-up. After randomization, participants will receive 28 sessions of acupuncture over a period of 12 weeks plus auricular acupressure or take Climen® (from Bayer Healthcare Company Limited, Guangzhou, China) tablets for three cycles. Acupuncture will be given as three sessions weekly in the first 4 weeks and two sessions weekly in the following 8 weeks for each patient. Each session will last 30 minutes. The follow-up period will last 24 weeks (13 to 36 weeks after randomization). Patients will be assessed before randomization as well as 4, 12, 16, 24 and 36 weeks after randomization.

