### Outcome measurement

The primary outcome of this trial is the MRS, which is widely used for evaluating the severity of aging symptoms. Eleven questions of the MRS can be classified into three categories: psychological, somatic, and urogenital. A higher score indicates worse symptoms. The primary outcome is measured at randomization and another five points (4, 12, 16, 24, and 36 weeks after randomization). The secondary outcomes include the following items: Menopause-Specific Quality of Life; average hot-flash score during 24 hours; and the level of estradiol, follicle-stimulating hormone, and luteinizing hormone in serum. The first two secondary outcomes are measured at randomization and 4, 12, 16, 24, and 36 weeks after randomization. The other secondary outcomes are measured before randomization and 12 and 24 weeks after randomization.

All patients are asked to fill in a 7-day hot flash diary before randomization and 4, 12, 16, 24, and 36 weeks after randomization. After treatment, patients will be encouraged to finish these diaries by short messages, telephone calls, and emails in order to avoid selective loss to follow-up.

To exclude patients who have serious heart, liver, and kidney diseases, all participants will also receive routine tests of blood, liver function, kidney function, and electrocardiogram before randomization. Patients will also receive breast ultrasound and gynecological B ultrasound to exclude some uncovered galactophore and gynecological diseases. Meanwhile, aiming to evaluate the side effects of both methods, participates will receive the following items after the end of treatment: breast ultrasound and gynecological B ultrasound; and liver function (alanine aminotransferase, aspartate aminotransferase) and kidney function (blood urea nitrogen, serum creatinine).

This study will also estimate the expectations of participants using the credibility and expectancy questionnaire, aiming to clarify whether expectations make an impact on outcomes.

All patients in this study are required to document whether or not they take other medicine to relieve their perimenopause-related symptoms during 36 weeks, including the name and dosage of the medicine, the time and duration of taking, the reasons and the side effects of the medicine.

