One recent RCT found that traditional acupuncture continued relieving the vasomotor symptoms throughout the 3-month treatment period, while the sham acupuncture was tending towards stability after the first month [17]. A longer duration of treatment was hypothesized to be a superior effect between traditional and sham acupuncture. Accordingly, in order to observe a significant effectiveness of acupuncture, participants in our study will receive 3 months of treatment. Another study indicated that the effectiveness of acupuncture on perimenopausal syndrome was superior to HRT during the 6-month follow-up period [43]. Therefore, it is necessary to conduct a longer period of follow-up to obverse the continuous effects of acupuncture compared with positive drug, and also to assess the safety after treatment. Before this trial we conducted a questionnaire survey of 156 women with perimenopausal syndrome in the First Affiliated Hospital of Chengdu University of TCM to obtain the public’s acceptance and understanding of acupuncture treatment for perimenopausal problems (the detail of this survey will be available soon). According to the results of the survey, previous RCTs and the opinions of experts, we designed this protocol for better treatment and follow-up arrangements.

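### Durability against the drug is a stated reason for follow-up to week 36, but no MRS contrast from end of treatment to week 24 or 36 is set, and divergence is judged from exploratory summary statistics on available data

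*Protocol article*

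**What the plan says.** All of this is in the protocol article.

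- **Purpose of follow-up (Discussions).** After citing a study in which acupuncture did better than HRT over six months of follow-up, the authors conclude that "it is necessary to conduct a longer period of follow-up to obverse the continuous effects of acupuncture compared with positive drug". The same sentence adds safety after treatment as a second purpose.
- **Schedule (Study design; Outcome measurement).** "The follow-up period will last 24 weeks (13 to 36 weeks after randomization"), and "The primary outcome is measured at randomization and another five points (4, 12, 16, 24, and 36 weeks after randomization").
- **Main model (Statistical analysis).** "The MRS is used as a dependent variable in an analysis of covariance, with the groups as random factors, and with baseline MRS and age". The last two enter the model for adjustment. Adjusted effects come with 95% CIs and P values in the intention-to-treat population, and the same method is applied to all secondary outcomes.
- **Missing data (Statistical analysis).** "Sensitivity analyses are performed for the primary outcomes (MRS measured 16 weeks after randomization) by replacing missing data with multiple imputations", and also by carrying observations forward. No other visit is mentioned.
- **Change over time (Statistical analysis).** As an exploratory addition to the ANCOVA, arm means across visits are described. "We will calculate summary statistics to reveal whether the two groups are changing in a similar or different fashion". The next sentence begins "A two-sided test is applied for available data" and sets the 5% significance level.

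**The concern.** Durability against the drug is a question about an arm-by-time difference: does the gap between the arms at week 36 differ from the gap when treatment ended at week 12? Arm means listed by visit do not estimate that quantity or give it a confidence interval. A difference that is significant at one visit and not at another is not evidence that the arms diverged.

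The second problem is who contributes to each mean. On available data, the set of women can change from visit to visit. MRS is scored so that lower is better, so if women with bad scores leave one arm, its later mean falls and looks like a sustained benefit. The limitations paragraph of the Discussions itself says that the 37-week period may raise dropout and that patients cannot be blinded, so unequal loss between arms is plausible.

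At stake is the interpretation of the later follow-up visits, not the primary week-16 result.

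**Working it through.** **1. No figure to reproduce.** The exploratory step carries no number. The inputs below are borrowed from Study population and sample size: SD 10, margin 4.5, 103 per arm, 20% dropout. Correlations between visits are not in the document. They are assumed and shown as a range.

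**2. What the ANCOVA already gives.** Write the model as y = a + τ·arm + β·baseline + error (age omitted for brevity). Subtracting baseline from both sides gives y − baseline = a + τ·arm + (β − 1)·baseline + error. The arm effect τ is the same. A check on one simulated data set of 206 women gave 0.3168 (SE 1.0962) for both forms. So wherever the ANCOVA is applied, it estimates a between-arm difference in change from baseline. That includes week 16, which lies inside the follow-up period of weeks 13 to 36.

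**3. What it does not give.** Let D12 and D36 be the arm differences at weeks 12 and 36. The durability contrast is D36 − D12, with

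Var(D36 − D12) = Var(D36) + Var(D12) − 2·Cov(D12, D36).

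Separate models by visit do not supply the covariance. It matters: with SD 10 at each visit, correlation r between the visits and n women per arm seen at both, the 95% half-width without covariate adjustment is 1.96 × 10 × √(2(1 − r)) × √(2/n). With n = 82 (103 × 0.8 = 82.4):

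| r | half-width (MRS points) |
|---|---|
| 0 (visits treated as independent) | 4.33 |
| 0.5 | 3.06 |
| 0.7 | 2.37 |

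**4. Size of the selective-loss problem.** Suppose the fraction q of one arm with the worst score at an earlier visit is missing later, and nobody is selectively lost from the other arm. For normal scores, the mean earlier score of those who remain falls by SD × φ(z)/(1 − q), where z is the (1 − q) quantile of the standard normal. A later score correlated r with the earlier one shifts by

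r × SD × φ(z)/(1 − q).

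- q = 0.20: z = 0.842, φ = 0.280, φ/(1 − q) = 0.350. Shift = 0.5 × 10 × 0.350 = 1.75, and 0.7 × 10 × 0.350 = 2.45.
- q = 0.10: z = 1.282, φ = 0.1755, φ/(1 − q) = 0.195. Shift = about 0.97 (r = 0.5) and 1.36 (r = 0.7).

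For scale only, 1.75/4.5 = 39% and 2.45/4.5 = 54% of the margin.

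**5. Where the stated protection stops.** Multiple imputation and carrying forward are stated for week 16 only. An ANCOVA run at week 24 or 36 on available data would condition on baseline and age, but not on the scores at weeks 4, 12 and 16 (or 24), which are the ones most likely to predict later loss.

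**The case against.** A reader might infer that the trial will estimate no between-arm difference in change at all. The document does not support that. The exploratory step is an addition to a baseline-adjusted ANCOVA with 95% CIs, and step 2 shows that this model estimates a difference in change. The sentence describing the model is not itself limited to week 16, so applying it to MRS at weeks 24 and 36 is a fair reading. The same method also covers all secondary outcomes, two of which are measured at weeks 16, 24 and 36. This part of the objection stands, and it is why the point is confined to what is specified for MRS beyond week 16.

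It would also be wrong to say that follow-up exists only for durability, since safety is named in the same sentence. Nor is loss ignored: Outcome measurement describes messages, calls and emails meant to prevent it. The exploratory paragraph is not purely descriptive either, since a two-sided test is mentioned, and the unnamed summary statistics could be per-patient measures compared between arms. Nowhere does the protocol say that it will read divergence from significance at one visit and not another.

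Finally, covariance structures and exploratory contrasts are usually left to an analysis plan, which is not shown. That would answer a complaint about missing detail. It does not fully answer this one, because the article does state how it will judge whether the arms change differently, and the stated method suits that question poorly.

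**Conclusion.** The point holds as a limited one. Beyond the ANCOVA, whose only named MRS time point is week 16, the stated basis for judging whether the arms change differently is exploratory arm means and unnamed summary statistics, with a test on available data. No MRS contrast from end of treatment to week 24 or 36 is set, and the missing-data sensitivity analyses stop at week 16.

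The shift of 1.75 to 2.45 points at 20% loss (0.97 to 1.36 at 10%) is a worst case for loss driven by one earlier score, not a forecast. It assumes normal scores, SD 10, correlations of 0.5 to 0.7 that the document does not give, and selective loss in one arm only. It applies to a raw available-data mean; baseline adjustment would remove part of it. The comparison with 4.5 only gives scale, because that margin belongs to the non-inferiority question. The primary analysis and the sample size are unaffected. The change is worth making because durability is a stated aim and the remedy is cheap.

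**What to change.** Keep the week-16 ANCOVA as it is. Replace the summary-statistics step with one repeated-measures model of MRS at weeks 4, 12, 16, 24 and 36:

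- fixed effects for arm, visit, arm-by-visit, baseline MRS, baseline-by-visit and age;
- unstructured covariance across visits.

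Report the arm differences at weeks 24 and 36, and the arm difference at week 36 minus that at week 12, each with a 95% CI. Plot the model-based means and keep the whole step labelled exploratory.

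The cost is a change of wording and one extra model on data already scheduled. Because the model uses every observed MRS score, it corrects for loss that depends on those scores. It does not correct for loss that depends on unobserved ones, and the report should say so.

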## Discussions

This trial is sponsored and financially supported by the National Key Technology R&D Program during the Twelfth Five-year Plan Period of China. The study reported in this article is only one part of this program, which is an international multicenter systematic evaluation of clinical effectiveness of acupuncture. The purposes of this international collaborative program are to prove the therapeutic effects and safety of acupuncture and to establish guidelines for clinical practice. The result of this trial is expected to provide convincing evidence that acupuncture is effective for patients with perimenopausal syndrome.

Previous RCTs show acupuncture in the treatment of symptoms of both perimenopausal and postmenopausal females has no advantage, compared with placebo needles [16-19]. Compared with no medical treatment (for example, self-caring, waiting), however, acupuncture is able to relieve symptoms quite well [16,17,29]. In view of controversial results, some researchers asserted that the placebo needles might have similar effects to verum acupuncture [30], and this view may underestimate the total effectiveness of verum acupuncture. We are therefore conducting a pragmatic trial that requires a positive drug as the control group to clarify an acupuncture therapeutic effect rather than a placebo needle. Moreover, we use a non-inferiority method to estimate the sample size, and only include perimenopausal patients. What we expect is to prove the therapeutic effects of acupuncture on perimenopausal syndrome, and provide another alternative treatment for perimenopausal women.

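### The trial is sized for non-inferiority with a 4.5-point MRS margin, but the Statistical analysis section never uses the margin and states only a two-sided P < 0.05 criterion

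*Protocol article*

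**What the plan says.** **Design and size.** Under Study population and sample size, the protocol article sets the margin: "we assume that a difference within 4.5 indicates acupuncture is not inferior to Climen® treatment". It then gives the sizing assumptions, "Using a non-inferiority design, and assuming a power of 90%, an alpha value of 5%, and a population standard deviation of 10", and concludes that "a total of 206 patients will be needed in this study", or 103 per group with 20% dropout allowed for. It does not say whether the 5% is one-sided or two-sided. The Discussions section repeats the framework: "we use a non-inferiority method to estimate the sample size".

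**Analysis.** Under Statistical analysis, the MRS is analysed by ANCOVA in the intention-to-treat population, with baseline MRS and age as covariates. The adjusted group effect is to be reported with a 95% confidence interval and a P value. Week 16 is identified as the primary time point. The next paragraph describes an exploratory analysis of group means over time and closes with "A two-sided test is applied for available data" and a 0.05 significance threshold. The section contains no non-inferiority hypothesis, no mention of 4.5, and no rule comparing a confidence limit with a margin.

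**The concern.** A two-sided test at P < 0.05 asks whether the arms differ. A non-inferiority trial asks whether AA could be worse than Climen by as much as the margin. The answers can diverge in both directions: a non-significant difference does not exclude a 4.5-point disadvantage, and a significant difference in favour of AA is not needed for non-inferiority.

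The article therefore states one hypothesis for sizing and a criterion for another in the analysis. At stake is the headline conclusion against a comparator that the article itself calls the gold standard. If the criterion is not tied to the margin beforehand, the choice between a P value and a confidence limit stays open until the results are known.

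**Working it through.** **Inputs, all from Study population and sample size:** margin 4.5, SD 10, power 90%, alpha 5%, 103 per arm, dropout 20%. The true difference assumed in sizing is not stated; I take 0. Evaluable per arm after dropout: 103 × 0.8 = 82.4, taken as 82. Differences are AA minus Climen, so positive values mean AA is worse.

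**1. Reproducing 206.** Per arm, n = 2 × [SD × (z(1−α) + z(0.90)) / margin]².

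- One-sided 5%: 2 × [10 × (1.645 + 1.282) / 4.5]² = 84.6, so 85 (86 with the t distribution). 86 × 1.2 = 103.2, so 103 per arm and 206 in total. This matches. Dividing 85 by 0.8 instead gives 107 per arm (214 in total).
- One-sided 2.5%: 103.8, so 104 per arm. This is close to 103 only if no dropout is allowed for. With 20% dropout it is 104 / 0.8 = 130 per arm (260 in total).

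The reading that fits all the stated inputs is a one-sided 5% non-inferiority test with dropout applied as × 1.2.

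**2. Standard error.** SE = 10 × √(2/n), which is 1.562 for n = 82 and 1.393 for n = 103.

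**3. The two criteria compared.**

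- P(non-significant) = Φ(1.96 − d/SE) − Φ(−1.96 − d/SE)
- P(non-inferiority by 95% interval) = Φ((4.5 − d)/SE − 1.96)

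| True difference d | n per arm | Two-sided P ≥ 0.05 | Upper 95% limit below 4.5 |
|---|---|---|---|
| 4.5 (at the margin) | 82 | 17.8% | 2.5% |
| 4.5 (at the margin) | 103 | 10.2% | 2.5% |
| 0 (arms equal) | 82 | 95% | 82.2% |
| 0 (arms equal) | 103 | 95% | 89.8% |

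For d = 4.5 and n = 82: 4.5 / 1.562 = 2.88, and Φ(1.96 − 2.88) = 0.178; the second term is negligible. If the arms are equal, the difference test is significant in favour of AA 2.5% of the time.

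**4. Where the criteria part.** With 82 per arm, the 95% half-width is 1.96 × 1.562 = 3.06. Non-inferiority then needs an observed disadvantage below 4.5 − 3.06 = 1.44. An observed disadvantage between 1.44 and 3.06 is non-significant, yet does not show non-inferiority.

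**5. Power of the interval rule.** Power = Φ(4.5/SE − z).

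| Interval | One-sided alpha | 82 per arm | 103 per arm |
|---|---|---|---|
| 90% | 5% | 89.2% | 94.4% |
| 95% (as planned) | 2.5% | 82.2% | 89.8% |

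**The case against.** The strongest reply is that the analysis already contains what is needed. The ANCOVA gives an adjusted difference with a 95% confidence interval, the margin is fixed elsewhere in the article, and comparing the two takes no new model or data. This stands. A reader might infer that the planned analysis cannot deliver a non-inferiority conclusion, and the documents do not support that. What is missing is the link between the interval and the margin.

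The two-sided-test sentence also closes the paragraph on exploratory analysis, so applying it to the primary outcome is an inference. That stands too. However, it is the only threshold in the section, and the primary P values have no other. If it is confined to the exploratory work, the primary analysis has no stated criterion, and the same repair is needed.

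A reader might also infer that P > 0.05 will be taken as equivalence, or that an observed difference below 4.5 will be enough. The article says neither. Its wording on the margin does not specify a point estimate or a confidence limit, and the power and alpha stated with it suggest an inferential test.

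Finally, a condensed article may leave the exact decision rule to an analysis plan that is not shown. Silence alone would be no finding. Here the article does state a criterion, and it is of the wrong kind for the stated design.

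**Conclusion.** The point holds as a mismatch between stated rules: the design and size are for non-inferiority, and the only criterion in the analysis section is a test of no difference.

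With AA truly at the margin, non-significance would occur about 18% of the time with 82 evaluable per arm, or about 10% if all 103 contribute. The false non-inferiority rate is 2.5% under a 95% interval rule, or 5% under a 90% one. These error rates describe what would follow if non-significance were read as non-inferiority; they do not describe a declared intention.

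A second issue follows from the first. The planned 95% interval does not match the alpha that best reproduces 206, so if it is used for the decision, power is about 82% after the assumed dropout, not 90%.

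The figures take the 4.5 margin as given and assume an SD of 10, a true difference of zero for power, and a normal approximation. Covariate adjustment may reduce the residual SD and raise power, but the article gives no baseline correlation, so the gain cannot be quantified.

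**What to change.** In the Statistical analysis section, state for the primary outcome that:

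- non-inferiority is concluded if the upper confidence limit for the adjusted MRS difference (AA minus Climen) at week 16 is below 4.5;
- P > 0.05 is not evidence of non-inferiority;
- superiority (P < 0.05 in favour of AA) is considered only after non-inferiority has been shown.

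Name the alpha in the same place and restate the power to match. A one-sided 5% rule (90% interval) agrees with the sizing and has about 89% power with 82 per arm. A one-sided 2.5% rule (the planned two-sided 95% interval) has about 82% with 82 per arm and about 90% with 103. State whether the two-sided sentence applies beyond the exploratory analysis.

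The change is wording only and needs no new data, model or patients. Its cost is that the stated power may become less favourable. Keeping 90% under the 95% interval after 20% dropout would take 260 patients on the sizing assumptions, so a sponsor who stays at 206 should report the lower figure openly. The wording should be settled before outcome data are examined.
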